### Interventions

#### Explanation of the choice of comparators {6b}

The active comparator (intervention) is a goal-directed care bundle that involves rapid correction (< 1 h) in those participants who have abnormal physiological and hematological variables during their in-hospital stay. The intervention includes early intensive BP lowering, glucose control, treatment of pyrexia, and reversal of previous use of anticoagulants. Sites without a formal institutional protocol on how to control BP, glucose, fever, and previous anticoagulants usage in acute ICH stage, or their protocol differentiated from the protocol provided in this study were eligible. Each site will keep their usual care or previous routine protocol before transferring to intervention phase. The usual care phase in place before switching to the intervention will act as the control comparator. The intention of introducing this intervention bundle is to enhance the implementation of guidelines or recommendations, narrow the gap between evidence and practice in LMICs, and improve outcome for patients with acute ICH. A one-direction stepped-wedge cluster design was used to allow all hospitals to change to improved systems of care.

#### Intervention description {11a}

The care bundle involves one or more components according to whether a participant has abnormal physiological or hematological parameters, as outlined below:
*Early intensive BP lowering*, where the goal is to achieve a target systolic BP level of < 140 mmHg within 1 h of initiation, and to maintain this level for the next 7 days, or hospital discharge should this occur earlier. Intravenous BP lowering is the preferred treatment to commence as soon as possible upon the patient’s admission. It is expected that intravenous therapy will continue to be required while any oral antihypertensive therapy is initiated, in order to maintain smooth BP control. A systolic BP of 130 mmHg is considered the lower threshold in which the treatment is to cease. Each site receives a standardized, stepped titratable, intravenous BP lowering protocol, based on available medications, that is established in advance.*Intensive glucose control*, where the goal is to achieve a target blood glucose level of 6.1–7.8 mmol/L and 7.8–10.0 mmol/L for without and with diabetes mellitus, respectively, and to maintain this level for the next 7 days, or hospital discharge should this occur earlier. In the intensive-treatment phase, a continuous infusion of insulin (50 international units [IU] in 50 mL of 0.9% sodium chloride for use in a pump) is recommended to be started as soon as possible if the blood glucose level exceeds 7.8 mmol/L and 10 mmol/L according to non-diabetes or diabetes, respectively. Adjustments of the insulin dose are based on measurements of whole-blood glucose, performed at 1- to 4-hourly intervals, with the aid of a glucose analyzer. Patients can be fed continuously with intravenous glucose at the time of admission, but total parenteral, combined parenteral and enteral, or total enteral, feeding is instituted the following day according to a standardized schedule whereby 20–30 non-protein kilocalories per kilogram of body weight per 24 h and a balanced composition (including 0.13 to 0.26 g of nitrogen per kilogram per 24 h, and 20 to 40% of nonprotein calories in the form of lipids) is achieved as early as possible.*Treatment of pyrexia*, where the goal is to achieve a body temperature level < 37.5 °C within 1 h of initiation and to maintain this level for the next 7 days, or hospital discharge should this occur earlier. Measurement of temperature is according to local practice. Patients allocated to the intensive group are to receive measures of their body temperature every 4 h over 72 h after admission. Patients with an increase (≥37.5 °C) in body temperature are to commence treatment as soon as possible, according to a standardized anti-pyrexia treatment protocol, based on available medications established in advance.*Reversal of anticoagulation*, where the goal is to achieve an international normalized ratio (INR) of < 1.5 within 1 h of treatment, and to maintain this level for the next 7 days, or hospital discharge should this occur earlier. All patients with ICH are to have a check of their blood INR immediately upon presentation. Those with an elevated INR (> 1.5) who are allocated to the intensive group should receive within 1 h of diagnosis: 5–10 mg of vitamin K administered slowly intravenously; and according to availability in the hospital, either intravenous fresh frozen plasma (FFP) at 20 mL/kg, after blood group typing or by using AB group plasma supplied by local transfusion units; or 30 IU/kg of intravenous four-factor prothrombin complex concentrate (PCC). The speed of the infusion of FFP or PCC should be as fast as the condition of the patient allows. Patients with an INR > 1.5 at 3 h after the start of treatment are to receive PCC (if INR ≤2.0, 10 IU/kg; if INR > 2.0, 30 IU/kg) as rescue treatment.

#### Criteria for discontinuing or modifying allocated interventions {11b}

All hospitals are randomly assigned to the intervention and encouraged to implement the intervention protocol as completely as possible. However, they may modify sections or skip them completely, according to clinical reasons.

#### Strategies to improve adherence to the intervention {11c}

The intervention protocol is given to investigators only after completion of control phase. An online training is organized for each site before starting the intervention. Regular intervention quality reports are provided to each site during intervention phase, and there is remote communication and on-site monitoring to improve the adherence to the intervention. Moreover, a process evaluation, designed to gain insights into the barriers and facilitators to change systems of care and implementation of the protocol, is undertaken through formative stakeholder engagement interviews during the course of the study.

#### Relevant concomitant care permitted or prohibited during the trial {11d}

Medical or surgical treatments besides those required within the care bundle are permitted during the study, but they need to be recorded in the case report form (CRF).

#### Provisions for post-trial care {30}

Not applicable. This study is evaluating a quality improvement protocol for use of interventions that are already available in routine practice which can potentially be sustained beyond completion of the study.

### Outcomes {12}

The primary outcome is functional recovery according to the modified Rankin scale (mRS) measured at 6 months and analyzed as an ordinal outcome (shift across all scoring categories of physical function that range from 0 to 5, and death as 6) [22].

Secondary outcomes include death or neurological deterioration according to a change in scores on the National Institute of Health stroke scale (NIHSS) [23] at 7 days, and poor outcome (defined by mRS scores 3–6), separately on death and disability (mRS scores 3–5), HRQoL using the EuroQoL Group 5-Dimension self-report questionnaire (EQ-5D) [24], duration of hospital stay, and residence, all measured at 6 months.

The safety outcomes of any all-cause and cause-specific serious adverse events (SAEs) are recorded according to standard definitions for the duration of follow-up.

### Participant timeline {13}

The schedule of randomization for sites as well as enrolment, treatment allocation, and assessments for participants is outlined in the Table 1 and Fig. 2.

**Table 1 Tab1:** Assessment schedule

Evaluation	Screen/enrolment log	Baseline	Day 1	72-h monitoring chart	7 days or hospital separation (discharge, transfer, or death)	6-month follow-up
**Forms**	**A**	**B**	**C**	**D/E**	**F**	**G**
Screen	X					
Eligibility	X					
Consent/re-consent	X					
Contact details	X					
Vital signs	X	X	X		X	
Physical parameters				X		
GCS		X				
NIHSS		X			X	
Medical history		X				
mRS					X	X
EQ-5D						X
Routine blood tests		X			X	
Brain imaging		X	X		X	
Standard stroke care		X			X	
Final diagnosis					X	
Medications in use			X	X	X	X
SAEs			X		X	X

*EQ-5D* EuroQoL Group 5-Dimension self-report questionnaire, *GCS* Glasgow Coma Scale, *mRS* modified Rankin scale, *NIHSS* National Institutes of Health stroke scale, *SAEs* serious adverse events

### Sample size {14}

The study is designed with 90% power (*α* = 0.05) to detect a 20% reduction in the odds (common odds ratio of 0.80) of worse functional outcome using ordinal logistic regression. Assuming a distribution of mRS in the usual care control arm that is similar to that observed in the standard BP control arm of the INTERACT2 study [7] (i.e., 7.6%, 18.0%, 18.8%, 16.6%, 19.0%, 8.0%, and 12.0% for mRS scores of 0 to 6, respectively), this corresponds to a 5.6% absolute improvement in the proportion of patients experiencing a poor outcome (mRS scores 3-6), that is from 55.6% down to 50%. This also translates into a 10% relative risk reduction (relative risk of 0.90). The combination of interventions as part of an intensive care bundle is assumed to provide a greater treatment effect than the use of BP lowering alone (in INTERACT2, the treatment effect was 4% absolute).

The study plans to recruit 110 sites in a stepped-wedge design consisting of 3 groups and 4 phases. Each group would, therefore, include approximately 36 sites. Assuming an intraclass correlation coefficient (ICC) of 0.044, which is similar to that of the INTERACT2 [7] and Head Position in Acute Stroke Trial (HeadPoST) [25] studies that included large numbers of hospitals in China, each site would be required to recruit an average of 18 patients per phase. Accounting for 5% of participants with a missing outcome, each site would need to target an average of 19 patients per phase, thus leading to a total sample size of 8360 patients (110 sites × 4 phases × 19 patients).

We recognize there will be variability in the number of patients who will be recruited at each site, with very large hospitals recruiting as many as 50 patients per phase while smaller hospitals may only recruit a few patients per phase. If the sample size was inflated to accommodate this issue as has been used in parallel cluster trials [26] (e.g., using an inflation factor of approximately 1.3), the sample size would need to reflect 25 patients per site per phase (i.e., 11,000 patients in total). However, given that this adjustment would be a very conservative scenario and that the effect of variability in cluster sizes is expected to be mostly mitigated by the randomization process, including stratification by size [27], we have elected to maintain the target average of 19 patients per site per phase for a total sample size of 8360 patients. Assuming a worst-case scenario for the effect of cluster size variability on power, this sample size would still provide at least 80% power to determine the proposed treatment effect.

### Recruitment {15}

All eligible ICH patients who present to each participating hospital from the start date are prospectively and consecutively enrolled into the study.

## Assignment of intervention: allocation

### Sequence generation {16a}

The unit of randomization is the hospital site, randomly assigned by a statistician not otherwise involved in the study using a pre-specified randomization schedule with permuted blocks. Participating sites are stratified according to country and the estimated recruitment capacity (ranging from 40, 80, 120, 160, and 200).

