## Statistics methods

### Statistical methods for primary and secondary outcomes {20a}

All analyses will be undertaken at the patient level on an intention-to-treat (ITT) basis at each site using generalized estimating equations (GEE) or random-effects regression to account for clustering. The primary outcome of a shift (improvement) in scores on the mRS at 6 months will be analyzed by means of an ordinal logistic regression, with mRS as a dependent variable with 7 levels (0 [no residual symptom] to 6 [death]). The model will include the trial phase (1 to 4), the randomized arm (control or intervention) corresponding to each phase, and the size of the site (as used in the stratification). The secondary outcome of neurological change at 7 days will be analyzed with the same method [28]. Binary and continuous secondary outcomes will be analyzed using a similar approach but using logistic and linear regression, respectively.

All analyses will be adjusted for clustering within center, hospital size (stratification variable), and for trial phase. In addition, sensitivity analyses will be conducted after considering potential prognostic variables as well as the effect of time to adjust for potential background secular trends, including the potential impact of the COVID-19 pandemic.

No adjustment for multiplicity is planned as there are only a small number of pre-specified efficacy outcomes being investigated. A detailed statistical analysis plan will be finalized before unblinding and database locked and posted on a pre-print server.

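### Country is a stratification factor in the site randomisation but is left out of the stated analysis models: a modest loss of precision, not a systematic bias

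*Protocol article*

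**What the plan says.** Under Sequence generation {16a}, hospitals are randomised with permuted blocks, and "Participating sites are stratified according to country and the estimated recruitment capacity", the latter in five levels. Study setting {9} lists ten countries and about 110 hospitals.

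Under Statistical methods for primary and secondary outcomes {20a}, the covariates are given twice. The primary ordinal model is to contain trial phase, arm, "and the size of the site (as used in the stratification"). The next paragraph extends this: "All analyses will be adjusted for clustering within center, hospital size (stratification variable), and for trial phase". Country appears in neither statement. Clustering is to be handled "using generalized estimating equations (GEE) or random-effects regression to account for clustering". The section also says that "sensitivity analyses will be conducted after considering potential prognostic variables as well as the effect of time to adjust for potential background secular trends", with COVID-19 named among the influences to be examined.

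**The concern.** The article's stated reason for putting size in the model is that it was a stratification factor. The same reason applies to country, yet country is absent and no explanation is given.

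Two things are at stake.

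- **Precision.** Without a country term, differences between countries count as between-site variance, and the standard error does not reflect the balance that the stratification has bought.
- **Chance imbalance.** Stratification limits imbalance but need not remove it. If the two factors are crossed, there are 10 × 5 = 50 strata for 110 sites, about 2.2 sites per stratum, to be spread over three step groups. Some blocks would then be incomplete, and site sizes within a country will differ. What imbalance remains is not adjusted for.

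The covariates are not left to the statistical analysis plan. The article fixes them and applies them to all analyses.

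**Working it through.** **Inputs from Sample size {14}.** "The study is designed with 90% power" at α = 0.05 (taken as two-sided), "common odds ratio of 0.80", the control mRS distribution 7.6/18.0/18.8/16.6/19.0/8.0/12.0%, 110 sites, 3 groups, 4 phases, ICC 0.044, and 18 evaluable patients per site per phase.

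**Assumptions, not in the article.** The share of between-site variance due to country is varied from 0 to 90%. Sites are split as 80 in one country and 30 over the other nine. Site sizes are equal for the power figures.

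**Step 1: reproduce the plan's figure.** Applying an odds ratio of 0.80 to the control distribution moves mRS 3–6 from 55.6% to 50.05%, as stated. With p̄ the average of the two distributions, Σp̄³ = 0.0272. The per-patient variance on the log-odds scale (Whitehead) is 3/(1 − 0.0272) = 3.084.

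- Within-site variance of a site-phase mean: s² = (1 − 0.044) × 3.084/18 = 0.1638
- Between-site variance: t² = 0.044 × 3.084 = 0.1357

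Hussey–Hughes variance, with groups of 37, 37 and 36 sites:

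Var = I·s²(s² + T·t²) / [(I·U − W)s² + (U² + I·T·U − T·W − I·V)t²]

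- I = 110, T = 4
- U = 37×3 + 37×2 + 36 = 221
- W = 37² + 74² + 110² = 18,945
- V = 37×9 + 37×4 + 36 = 517
- I·U − W = 5,365
- U² + I·T·U − T·W − I·V = 48,841 + 97,240 − 75,780 − 56,870 = 13,431

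Var = 12.73/(878.7 + 1,822.4) = 0.00471, so SE = 0.0686. Power = Φ(0.2231/0.0686 − 1.96) = 90.2%. At 17 per site-phase it is 88.6%, so 18 is the smallest number that reaches 90%. Then 18/0.95 = 18.95, rounded to 19, and 110 × 4 × 19 = 8,360. The plan's figure is reproduced.

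**Step 2: add country.** This uses generalised least squares on site-phase means with a random site intercept, with and without country fixed effects. Power is computed from the SE that each model would report.

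| Country share of between-site variance | Variance ratio, with/without country | Power with country |
|---|---|---|
| 0% | 1.002 | 90.1% |
| 25% | 0.974 | 90.9% |
| 50% | 0.932 | 92.0% |
| 75% | 0.862 | 93.8% |
| 90% | 0.790 | 95.5% |

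For example, at 50% the SE is 0.0686 × √0.932 = 0.0663, and Φ(0.2231/0.0663 − 1.96) = 92.0%. Without country, the reported SE gives 90.2% throughout.

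Part of the gain is a correction of the reported SE. At a 50% share, the actual sampling variance of the model without country, under stratified allocation, corresponds to 91.4%. So of the gap from 90.2% to 92.0%, about 1.2 points arise because the reported SE is too wide, and about 0.6 point is true efficiency.

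**Step 3: does leaving country out shift the estimate?** This was simulated over 300 allocations stratified by country, with unequal site sizes and an assumed country difference of 0.5 log-odds. The target log odds ratio is 0.223.

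| Model without country | Mean shift | SD of shift |
|---|---|---|
| Random site intercept | 0.0005 | 0.006 |
| GEE, independence | 0.0002 | 0.038 |

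The mean shift is negligible in both. The scatter is 0.006/0.223, about 3% of the target, under a random intercept, and 0.038/0.223, about 17%, under GEE independence. With country in the model it is zero. The simulated allocation was not stratified by site size, as the trial's is, so 0.038 may be somewhat high.

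**Step 4: would country adjust for start date?** With an assumed trend of −0.01 log-odds per month and later starts outside the main country, the SD of the shift under a random intercept is 0.004 without country and 0.005 with it. A country term brings no gain there. Under GEE independence the SD falls from 0.022 to 0.014.

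**The case against.** The case against is substantial. The trial reaches its 90% target without country. Error in the reported SE is on the conservative side, and no inflation of the type I error follows. The size of the gain rests on a country share that the article does not give. The ICC of 0.044 is described as similar to that in studies with many hospitals in China. If most variation lies between hospitals within a country, a country term removes little, and at a share of zero it costs about 0.1 power point. The unseen statistical analysis plan may already include country. All of this limits the size of the point and stands. It does not remove the mismatch between two sections of the same article.

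Three stronger readings are tempting, and the article supports none of them.

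- **A reader might infer that the treatment estimate is biased by country differences.** Allocation is stratified by country, every site contributes both conditions, and a random site intercept takes up most of a difference that is constant within a site.
- **A reader might infer that the omission leaves start dates unadjusted and that adding country would cure this.** China began in December 2017 and the other countries later, but a country intercept does not model calendar time within a site. The article plans sensitivity analyses for secular trends and COVID-19.
- **A reader might take country to be the more important of the two factors.** No figure in the article shows this.

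**Conclusion.** The point holds in a limited form. The site randomisation is stratified on two factors, and the stated models carry one of them. The consequence is a possible loss of precision of about 0 to 2 power points if country explains up to half of the between-site variance, and about 5 points at an extreme share of 90%. Chance scatter from country imbalance is small under a random site intercept and matters mainly under GEE with an independence working correlation, which the article neither chooses nor excludes. These sizes rest on the assumed country shares, the assumed split of sites by country, the assumed 0.5 log-odds country difference and a linear approximation to the ordinal model. The mismatch itself rests on no assumption.

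**What to change.** Add country as a fixed effect to the primary and secondary models, alongside site size, phase, arm and site clustering, and bring the covariate statements in {20a} into line with {16a}. Before unblinding, set a rule that pools countries with very few sites into a region, so that the ordinal model can be fitted. If country is left out on purpose, say why.

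The cost is a sentence or two in the analysis plan, up to 9 degrees of freedom for ten countries, and about 0.1 power point if country turns out to explain nothing. The country term should not be presented as an adjustment for start date or calendar trend. The planned secular-trend sensitivity analyses are still needed for that.

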### Concealment mechanism {16b}

A statistician not otherwise involved in the study will randomly allocate hospitals into 3 groups, with each group to assign the time of switching from usual care (control) to care bundle (intervention) across hospital sites. The randomization group will be notified to the site within 2 weeks of the agreed date of commencing the phase of study. All eligible ICH patients presenting to participating hospitals from the start date will be prospectively and consecutively enrolled, and when assigned to the intervention phase will be managed with the care bundle as usual clinical practice.

### Implementation {16c}

In phase 1, all hospitals will be observed under usual care “control” conditions according to usual management of ICH patients. In phase 2, the first cluster of hospitals (group 1) will start implementing the intervention (care bundle), and then sequentially, groups 2 and 3 will start implementing the interventional package in phases 3 and 4, respectively, so that by phase 4, all hospitals will be receiving the intervention, with those in group 1 having the intervention for longest and those in group 3, the shortest. Once the site has completed the necessary control usual care observational period, they will receive training on the application of the care bundle intervention during the study. The site investigator will be informed to pause enrolment when the patient number or study duration in control phase has reached the pre-specified target, and then will be instructed to transfer over to the intervention phase after a recruitment interval of 7–10 days.

## Assignment of interventions: blinding

### Who will be blinded {17a}

The treatment is open label to both investigators and patients at sites. All other investigators, statisticians, and endpoint assessors are blind to the treatment allocation, who are trained to collect outcome measures by telephone at 6 months.

### Procedures for unblinding if needed {17b}

Not applicable. This study is an unblinded, hospital-level intervention.

## Data collection and management

### Plans for assessment and collection of outcomes {18a}

Hospitals are required to collect data on participating patients at admission (baseline), 72 h monitoring chart, separation (day 1; day 7 or at discharge if earlier, transfer from the hospital or death), and all SAEs including death until the 6 months of follow-up. The 6-month assessments will be conducted by an appropriately trained independent outcome assessor, using an assigned telephone script and kept blind to the treatment allocation. The assessor will be managed by the regional office in each country.

Table 1 illustrates the schedule and nature of the data collection required during the study period.

